### Provisions for post-trial care

There is no anticipated harm and compensation for trial participation.

### Sample size

According to studies conducted by Hong SB et al. and Roustan A et al., the clinical pregnancy rate of DOR patients is respectively 20.6% and 20.2% [16, 17]. Due to the lack of effective randomized blinded controlled clinical trials that choose clinical pregnancy rate per cycle as the primary outcome measure in evaluating acupuncture efficacy, we presume 15% for the patient's clinical pregnancy rate per cycle. Assuming that the clinical pregnancy rate can be increased by 15% after acupuncture treatment, *α*=0.05, *β*=0.20, power is 80%. The sample size is calculated according to the following formula [18], nA=κnB, nB=[pA(1-pA)/κ+pB(1- pB)](z1-α/2+z1-β)2/(pA-pB)2,*κ*=1, then we get nA=nB=135,which means the sample size of each group is 135. Allowing for a 20% dropout rate, the sample size of this trial is 338 participants.

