### Statistical methods

All analyses will be based on the intention-to-treat principle. Data analysis will be performed by an independent statistician using SAS statistical software (version 9.4; SAS Institute Inc.).

The analysis of variance (ANOVA) will be used to test the difference of clinical pregnancy rate (primary outcome) between the two intervention groups with the baseline date as a variate and taking into account the multicenter effect. Missing data will be imputed using the multiple imputation method. Continuous data will be presented as the mean and standard deviation, or the median and interquartile range. Categorical data will be presented as the number and percentage. Comparisons between groups will be analyzed using an independent *t* test or Wilcoxon rank-sum test for continuous variables, and a chi-square test or Fisher exact test for categorical variables. All statistical tests will be two-sided, and *p* < 0.05 will be considered statistically significant.

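### The stated inputs and printed formula give 118 per group, not 135, so the control rate, the power or the formula is misreported

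*Protocol article*

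**What the plan says.** The Sample size section gives the whole calculation in one paragraph.

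- **Literature rates.** Two cited studies are reported: "the clinical pregnancy rate of DOR patients is respectively 20.6% and 20.2" (per cent).
- **Planning rate.** Pointing to a lack of suitable blinded acupuncture trials with this endpoint, the authors write "we presume 15% for the patient's clinical pregnancy rate per cycle".
- **Effect.** "Assuming that the clinical pregnancy rate can be increased by 15% after acupuncture treatment". The text does not say whether this is in percentage points or relative.
- **Error rates.** Alpha is 0.05, beta 0.20 and power 80%. The printed formula uses the two-sided critical value, and Statistical methods confirms that "All statistical tests will be two-sided".
- **Formula.** It is the unpooled two-proportion formula with 1:1 allocation and no continuity correction.
- **Result.** "then we get nA=nB=135,which means the sample size of each group is 135".
- **Dropout.** "Allowing for a 20% dropout rate, the sample size of this trial is 338 participants".

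**The concern.** Inputs, formula and result are all printed and legible, so the calculation can be repeated exactly, and it does not come out. The gap is 17 per group: 135 is 14% above 118 (135/118 = 1.144), too much for rounding.

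The control rate, target difference and power are the figures against which the primary result, and a null result in particular, will be read. As printed they do not agree with each other. A reader cannot tell whether the trial was planned on a control rate of 15% or about 20%, or for 80% or 85% power. Anyone who plans a similar trial from the printed inputs would arrive at 118 per group. If the true control rate were 20%, with the same 15-point difference, 118 per group would have only about 74% power.

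**Working it through.** **Inputs** (Sample size section; two-sidedness also from Statistical methods): control rate pB = 0.15; treatment rate pA = 0.15 + 0.15 = 0.30; two-sided alpha 0.05, z = 1.960; power 80%, z = 0.842; allocation ratio 1.

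**Printed formula, 1:1 allocation:** n = [pA(1−pA) + pB(1−pB)] × (z for alpha + z for power)² / (pA−pB)².

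**Stated inputs:**
- Variance term: 0.30 × 0.70 + 0.15 × 0.85 = 0.2100 + 0.1275 = 0.3375.
- (1.960 + 0.842)² = 7.849.
- n = 0.3375 × 7.849 / 0.0225 = 117.7, so 118 per group.

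The stated 135 is not reproduced.

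**Dropout step.** From 135: 270/0.8 = 337.5, so 338, as stated. This step is correct, so the fault lies in the 135 or in what produced it. From 118: 236/0.8 = 295, or 296 if each group is rounded up (118/0.8 = 147.5, so 148 × 2).

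**What would give 135?**

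| Rates | Power | Formula | n per group |
|---|---|---|---|
| 15% v 30% | 80% | printed | 117.7 |
| 15% v 30% | 80% | printed, but one-sided | 92.7 |
| 15% v 30% | 80% | arcsine | 118.6 |
| 15% v 30% | 80% | pooled, no correction | 121 |
| 15% v 30% | 80% | printed, with continuity correction | 130.7 |
| 15% v 30% | 80% | pooled, with continuity correction | 134 |
| 15% v 30% | 85% | printed | 134.7 |
| 15% v 30% | 90% | printed | 157.6 |
| 20% v 35% | 80% | printed | 135.2 |

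The two close matches from the printed formula:
- 20% v 35%, 80% power: (0.1600 + 0.2275) × 7.849 / 0.0225 = 135.2.
- 15% v 30%, 85% power: 0.3375 × (1.9600 + 1.0364)² / 0.0225 = 134.7.

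Solving the printed formula for n = 135 gives a control rate of 19.9% (80% power, 15-point increase), or a power of 85.1% (15% v 30%).

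**Power at 135 per group**, printed (unpooled) variance:
- 15% v 30%: standard error √(0.3375/135) = 0.0500; 0.15/0.0500 − 1.96 = 1.04; power 85.1% (84.3% with the pooled variance).
- 20% v 35%: standard error √(0.3875/135) = 0.0536; 0.15/0.0536 − 1.96 = 0.84; power about 79.9% (79.2% pooled).
- At the cited rates plus 15 points: 79.8% from 20.2% and 79.4% from 20.6%.

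**The case against.** The strongest reply is that this is a drafting slip in a trial that is large enough. Much of that stands. On the literal inputs 338 is conservative, since about 295 would do. If the control rate was really about 20%, power is still essentially 80%. Enrolment, alpha and the analysis are unaffected. The reason given for 15%, the lack of acupuncture trials with this endpoint, suits an assumed treatment effect better than a control rate, so the first 15% may be a garbled statement of the increment. That is plausible, but it is inference: the text gives 15% as the rate, and nothing elsewhere in the article corrects it.

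A reader might go further than the article allows in four ways.

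- **That the error must lie in the control rate or the power.** The list is not complete. The pooled formula with continuity correction gives about 134 for 15% v 30% at 80% power, so the formula could be the misreported item, although the article says the uncorrected one was used.
- **That 20% was certainly the planning rate.** It fits the cited 20.2% and 20.6%, but the fit is not exact. 135.2 becomes 136 if rounded up, and the cited rates themselves give 135.8 and 137.0.
- **That the target effect is unknown.** All three reconstructions share the same difference of 15 percentage points; what differs is the base rate, the power or the formula.
- **That a relative increase was meant.** Going from 15% to 17.25% would need about 4,190 per group, which cannot be reconciled with 135. The missing unit is a matter of wording only.

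**Conclusion.** The point holds as an internal inconsistency in the sample size basis: the printed inputs in the printed formula give 118 per group where 135 is stated. At least one of the control rate, the power and the formula is misreported, and the article does not settle which.

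The article does not support a conclusion that the trial is materially underpowered. On the three readings that come close to 135, power is about 80% to 85%. This rests on reading the increase as 15 percentage points, on two-sided testing at 0.05, and on 135 evaluable participants per group after dropout. The harm is to the justification and to how the result will be read. It needs correcting because these are the trial's declared planning figures, but the correction is to the text and not to the design.

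**What to change.** Keep the enrolment target of 338. Before unblinding, go back to the original calculation and restate, as actually used:

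- the control rate;
- the increase, in percentage points;
- the power;
- the formula, including any pooling, continuity correction and rounding.

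Together these should reproduce 135. They should come from the record of the calculation and should not be picked because they return the right number. If 15% v 30% and the printed formula are confirmed, change the stated power to about 85%. If the control rate was about 20%, correct the 15% and link it to the cited rates. If another formula was used, print that one.

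The cost is one or two corrected sentences, with no change to enrolment or analysis. Doing it before unblinding avoids any appearance that the planning figures were chosen in the light of the results.

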### Recruitment

Eligible patients will be recruited from participating hospitals through the following strategies. Posters will be placed on doctors’ offices, bulletin boards, or other places in the hospitals. Advertisements are also put via network, Wechat, etc. Eligible patients from the outpatient and inpatient clinics will be advised by doctors. In each hospital, specialized staff will contact patients and make an appointment for a screening visit.

### Blinding

In this study, participants, outcome assessors, and statisticians are blinded. The acupuncturists will not be blinded.

Many efforts will be done to maintain blinding in participants assigned to the intervention and control groups. For example, eligible patients will be acupuncture naïve. In the control group, electrodes are connected to the needles, which is the same as the intervention group, but the stimulators should be turned on at an intensity of zero.

We will also try to ensure that the outcome assessors and statisticians are unaware of the group allocation. The two groups will be labeled as groups 1 and 2. Assessors will be randomly assigned to follow-up. Allocation sequence will be concealed until the end of the study. In addition, we will separately give relevant data of AEs, and AES to an independent statistician for analysis, while the statistician responsible for the analysis of primary outcome and other secondary outcomes will be blinded to group allocation.

After the patients completed the whole visit, they will be told which group they were allocated in.

### Data management and quality control

Researchers including acupuncturists, outcome assessors, and statisticians will receive training about data management. In this trial, online monitoring will be used. Data of participants will be inputted into the electronic case report form (eCRF) through clinical trial management public platform called ResMan. The clinical research associates are responsible for verifying the accuracy of data. All the research documents, which include both the paper files and electronic documents, will be preserved for at least five years after publication. The private information of patients (name, telephone number, and ID number) will be anonymous to ensure participant confidentiality. After approval of a proposal and with a signed data access agreement, researchers whose proposed use of the data has been approved can have access to the data.

The quality controller of each hospital will complete self-inspection at least once every month. Remote or onsite monitoring will be performed for all centers once per 3 months by the principle investigator. The auditing will be done by DMC (Clinical Research Center of Tongji hospital) at the beginning, middle, and end of the trial. The DMC was established in 2018, which consists of investigators, data managers, biostatisticians, and study coordinators. The DMC is independent of the study organizers. The responsibility of DMS is periodically reviewing the accumulating data and determining if this trial should be modified or discontinued. The DMC does not have executive power; rather, it communicates the outcome of its deliberations to the trial sponsors. The chair is [name], with [name], [name]. For patients who deviate from the trial, causes and relevant outcome data will be recorded in a case report form as much as possible.

### Statistical methods

All analyses will be based on the intention-to-treat principle. Data analysis will be performed by an independent statistician using SAS statistical software (version 9.4; SAS Institute Inc.).

The analysis of variance (ANOVA) will be used to test the difference of clinical pregnancy rate (primary outcome) between the two intervention groups with the baseline date as a variate and taking into account the multicenter effect. Missing data will be imputed using the multiple imputation method. Continuous data will be presented as the mean and standard deviation, or the median and interquartile range. Categorical data will be presented as the number and percentage. Comparisons between groups will be analyzed using an independent *t* test or Wilcoxon rank-sum test for continuous variables, and a chi-square test or Fisher exact test for categorical variables. All statistical tests will be two-sided, and *p* < 0.05 will be considered statistically significant.

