### Outcome measures

#### Primary outcome measure

The primary outcome is clinical pregnancy rate per cycle of IVF-ET after acupuncture (through study completion, an average of 1 year). Clinical pregnancy was defined by the presence of a fetal heartbeat at 6–7 weeks of pregnancy. The clinical pregnancy rate is the number of clinical pregnancies per embryo transfer cycles.

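### Intention-to-treat is paired with unrestricted multiple imputation and a per-transfer outcome, so a randomised woman who never reaches transfer is excluded or imputed, and no rule counts her as not pregnant

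*Protocol article*

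**What the plan says.** Three statements in the protocol article bear on this point.

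- **Statistical methods** sets the analysis principle: "All analyses will be based on the intention-to-treat principle". After the sentence on the primary analysis it gives the missing-data rule: "Missing data will be imputed using the multiple imputation method". It does not limit the rule to particular outcomes or say who counts as missing. It names no imputation model or missingness assumption.
- **Primary outcome measure** fixes the denominator: "The clinical pregnancy rate is the number of clinical pregnancies per embryo transfer cycles".
- **Sample size** sets the planning figures: "we presume 15% for the patient's clinical pregnancy rate per cycle", "Assuming that the clinical pregnancy rate can be increased by 15% after acupuncture treatment" and "Allowing for a 20% dropout rate, the sample size of this trial is 338 participants". It gives no timing, reason or split by arm for the dropout.

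IVF-ET comes after an acupuncture course of 8 to 12 weeks (Interventions; IVF-ET treatment), and cycle cancellation is a listed secondary outcome (Outcomes of IVF). Women without a transfer are therefore expected. No section says that such a woman counts as not pregnant.

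**The concern.** Intention-to-treat asks what happens to women assigned to electro-acupuncture compared with women assigned to sham. A woman who leaves before IVF, or whose cycle is cancelled before transfer, is part of that question, and her answer on the primary outcome is known: no pregnancy by IVF-ET. The article offers two routes for her. Under the outcome definition she is outside the denominator. Under the missing-data sentence, if she is regarded as missing, her result is imputed. Imputation that is missing-at-random within arm would draw it from women in her arm who had a transfer.

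Both routes describe women who reach transfer. The first compares groups selected after randomisation. The second adds pregnancies that did not occur and gives active-arm dropouts the full treated rate. At stake are the size and meaning of the primary estimate, which would be reported as intention-to-treat.

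**Working it through.** **Inputs.** From Sample size: control rate 15%; increase of 15, read as percentage points (a relative increase of 15% could not give 135 per arm), so 30% in the active arm; 135 evaluable per arm; 20% dropout; 338 in total, or 169 per arm. From Statistical methods: two-sided testing at 0.05. Assumed, because the article does not say: when dropout occurs, how it splits by arm, and how many dropouts become pregnant.

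**The plan's own figure.** 270 / 0.8 = 337.5, rounded up to 338, which matches. The 135 per arm is matched to within one by the pooled formula with continuity correction (134). The formula as printed gives (0.15 × 0.85 + 0.30 × 0.70) × 7.849 / 0.15² = 117.7, or 118. That discrepancy does not affect what follows.

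**Base case: 20% dropout in each arm, all before IVF-ET, none pregnant.**
- Imputation within arm: 30% − 15% = 15 points.
- Counted as not pregnant: 0.8 × 30% − 0.8 × 15% = 24% − 12% = 12 points.
- Ratio: 15 / 12 = 1.25. A simulation (169 per arm, 2000 trials, 20 imputations) gave 0.149 against 0.119, the same ratio.
- Risk ratio: 30/15 = 24/12 = 2.0 either way.
- Imputed pregnancies: 0.2 × 169 = 33.8 dropouts per arm; 33.8 × (0.15 + 0.30) = 15.2. Observed: 135.2 × 0.45 = 60.8. So 15.2 / 76.0, or 1 in 5 counted pregnancies, would be imputed.

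**Varying the assumptions.** With dropout d_C (control) and d_T (active) and no pregnancies among dropouts, the effect of assignment is 0.30(1 − d_T) − 0.15(1 − d_C). Imputation within arm targets 15 points in every row.

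| Scenario | Effect of assignment | Imputed 15 points is |
|---|---|---|
| 10% in each arm | 13.5 | 11% too high |
| 20% in each arm | 12.0 | 25% too high |
| 20% in each arm, half leave without IVF, the rest have the completers' rate | 13.5 | 11% too high |
| 20% in each arm, all have the completers' rate | 15.0 | correct |
| Control 15%, active 25% | 9.75 | 54% too high |
| Control 25%, active 15% | 14.25 | 5% too high |
| Control 30%, active 10% | 16.5 | 9% too low |

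**Two other cases.** If active-arm dropouts revert to the control rate and control dropouts keep theirs, the effect is 0.15 × (1 − d_T), which is 12 points at 20% (27% versus 15%). If treatment arm is left out of the imputation model, the estimate is 0.8 × 15 = 12 points, so there is no overstatement in the base case.

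**Power with 169 per arm.** For 12% versus 24%, SE = √[(0.12 × 0.88 + 0.24 × 0.76)/169] = 0.0413; 0.12/0.0413 − 1.96 = 0.95, giving about 83%. In the concern's simulation of 4000 trials, imputation within arm gave about 86%. The effect on the test is small.

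**The case against.** The strongest reply is that the missing-data sentence is generic. It does not say that a woman without a transfer is missing, or that imputation is within arm under missing-at-random. A journal article normally leaves such detail to a full protocol or analysis plan, which is not shown. Moreover, if her result is known, a rule for missing data need not reach her. The article also plans to observe these women: it follows non-pregnant women for a year (Follow-up detection) and records outcome data after deviation as far as possible (Data management and quality control). Stopping acupuncture does not prevent a later transfer.

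Much of this stands. The absence of imputation detail is not the defect. A reader might also infer that the plan will overstate the benefit by a quarter, or that the bias always favours electro-acupuncture. The article supports neither, because it gives no timing or split for its 20% and no imputation model, and the table shows zero bias and a reversal. Nor does it require completion of the acupuncture course before an outcome counts.

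The reply does not remove the conflict in the text. If the missing-data rule does not reach a no-transfer woman, the per-transfer denominator excludes her, which also departs from intention-to-treat. Changing the denominator alone would leave it open whether the added women are imputed.

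**Conclusion.** The point holds as a conflict between three stated rules: intention-to-treat, unrestricted multiple imputation, and an outcome defined per transfer cycle. Together they leave no route by which a randomised woman without a transfer is counted as not pregnant, so the primary estimate would describe women who reach transfer.

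The size is conditional. The 25% overstatement of the risk difference needs imputation within arm, together with either 20% dropout that is equal by arm, all before IVF-ET and all not pregnant, or active-arm dropouts reverting to the control rate. If only half of an equal 20% leave without IVF it is 11%. Other patterns range from 54% too high to 9% too low. The harm lies in the estimate and its label. The risk ratio is unchanged at equal dropout with none pregnant, and power moves little. This should be settled before unblinding.

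**What to change.** For the primary outcome, replace the missing-data sentence and align the outcome definition with it:

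1. The primary analysis includes all randomised women.
2. A woman known to have had no IVF cycle or no transfer counts as not pregnant by IVF-ET and is not imputed.
3. Multiple imputation is limited to women whose pregnancy status is truly unknown.
4. A sensitivity analysis counts all unknown results as not pregnant. Control-based imputation may be added as a second one.

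Control-based imputation is better kept out of the primary analysis. It is a debatable choice of estimand, and it requires the control arm to be identified, whereas the Blinding section labels the arms 1 and 2 and keeps the primary-outcome statistician blinded.

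The cost is wording and one or two extra analyses, with no additional patients or data. The downside is a smaller expected risk difference: about 12 points instead of 15, with power about 83% at 169 per arm under the base-case assumptions, which is still above the planned 80%.

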#### Secondary outcome measures

##### The change of ovarian reserve function

Assessing patients’ ovarian reserve function before and after acupuncture intervention (at 0 weeks and up to 12 weeks), including:
The serum AMH, inhibin, and FSH and E2 levels on the third day of menstruation;AFC.

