##### Blood biochemical index examination before and after acupuncture

The level of blood corticotrophin-releasing hormone (CRH), norepinephrine, adrenaline, 5-hydroxytryptamine, beta-aminobutyric acid (GABA), dopamine (DA), and neuro-endorphin will be tested before and after treatment (at 0 weeks and up to 12 weeks).

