##### Questionnaires

Evaluation of anxiety, depression, and quality of life will be performed before and after treatment (at 0 weeks and up to 12 weeks), including:
Baker anxiety self-rating scale (BAI) and baker depression self-rating scale (BDI-II): higher score indicates higher degree of depression or anxiety [12, 13].Zung anxiety self-rating scale (Zung-SAS), Zung depression self-rating scale (Zung-SDS) [14, 15].Quality of life measurement (QOL): Quality of life will be assessed by SF-36 and the Chinese quality of life scale (CHQOL).

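### Continuous secondary outcomes that have a week-0 value are given only unadjusted t or rank-sum tests, so baseline is either ignored or used inefficiently

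*Protocol article*

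**What the plan says.** Statistical methods in the protocol article treats two groups of outcomes differently.

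- **Primary outcome.** Clinical pregnancy rate is analysed "with the baseline date as a variate and taking into account the multicenter effect" (I read the word 'date' there as 'data').
- **Other continuous variables.** The between-group comparison is an independent *t* "test or Wilcoxon rank-sum test for continuous variables". No covariate is named and centre is not mentioned. On direction, the section says "All statistical tests will be two-sided".

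Three sets of secondary outcomes have a value before treatment and one after it:

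- AMH, inhibin, FSH, E2 and AFC, under the heading "The change of ovarian reserve function": "Assessing patients’ ovarian reserve function before and after acupuncture intervention (at 0 weeks and up to 12 weeks".
- Seven blood markers, in the section on blood biochemical index examination: "will be tested before and after treatment (at 0 weeks and up to 12 weeks".
- BAI, BDI-II, Zung-SAS, Zung-SDS, SF-36 and CHQOL, under Questionnaires: "Evaluation of anxiety, depression, and quality of life will be performed before and after treatment (at 0 weeks and up to 12 weeks".

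The article does not state whether the t or rank-sum test is applied to the post-treatment value or to the change. Only the heading for ovarian reserve gives a hint, and it points to change.

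**The concern.** The trial will hold a week-0 value for each of these outcomes. The plan already accepts baseline and centre adjustment in principle, since it uses both for the primary outcome, but it then fixes an unadjusted two-sample test for the continuous outcomes.

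If post-treatment values are compared, the baseline measurement does nothing. If changes are compared, baseline enters with its coefficient fixed at 1 rather than at the value the data support, which costs precision whenever the correlation is below 1. In both cases a chance difference between arms at week 0 carries over in part to the estimated effect.

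At stake is how precisely the trial can report on the hormonal markers, the biochemical markers and the patient-reported scales. The sample size was set for pregnancy rate only, so an efficient analysis is the cheapest way to improve precision on these outcomes.

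**Working it through.** **Inputs from the article**

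- n = 135 per group, two-sided alpha 0.05, power 80% (Sample size, Statistical methods).
- The article states no power, SD or correlation for any secondary outcome, so there is no figure of its own to reproduce on this point.
- The 135 is used only as a reference size. It is the number before the dropout allowance: 135/(1 − 0.20) = 168.75, so 169 per group and 338 in total, as stated.

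**Assumptions**

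- Baseline to follow-up correlation r between 0.3 and 0.8.
- Equal variance at both visits, and a linear relation.
- One degree of freedom for the baseline slope, negligible at this size.

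**Variance of the treatment contrast**, relative to a t test on post-treatment values:

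- ANCOVA: 1 − r²
- t test on change: 2(1 − r)
- ANCOVA relative to change: (1 − r²)/[2(1 − r)] = (1 + r)/2

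**Reference difference.** With 135 per group, a t test on post-treatment values has 80% power for (1.960 + 0.842) × √(2/135) = 0.341 SD. The power columns below apply to that same difference.

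| r | ANCOVA vs post | Change vs post | ANCOVA vs change | Power, post | Power, change | Power, ANCOVA | Detectable by ANCOVA (SD) |
|---|---|---|---|---|---|---|---|
| 0.3 | 0.91 | 1.40 | 0.65 | 80% | 65.8% | 83.6% | 0.325 |
| 0.5 | 0.75 | 1.00 | 0.75 | 80% | 80.0% | 89.9% | 0.295 |
| 0.6 | 0.64 | 0.80 | 0.80 | 80% | 87.9% | 93.8% | 0.273 |
| 0.7 | 0.51 | 0.60 | 0.85 | 80% | 95.1% | 97.5% | 0.244 |
| 0.8 | 0.36 | 0.40 | 0.90 | 80% | 99.3% | 99.7% | 0.205 |

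Example at r = 0.5: power of ANCOVA = Φ(2.802/√0.75 − 1.960) = Φ(1.275) = 89.9%.

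So ANCOVA removes 9% to 64% of the variance of a post-value test and 10% to 35% of the variance of a change test. The two gains run in opposite directions: a high r favours ANCOVA over post values, a low r favours it over change. Below r = 0.5 a change score is less precise than ignoring baseline altogether. ANCOVA is at least as precise as either across the range, so the choice need not wait for an estimate of r.

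**Chance imbalance.** The standard error of a baseline difference is √(2/135) = 0.122 SD. Take an imbalance of 1.5 standard errors, 0.183 SD. It shifts a post-value comparison by r × 0.183 and a change comparison by (r − 1) × 0.183:

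- r = 0.7: post 0.128 SD, change −0.055 SD
- r = 0.3: post 0.055 SD, change −0.128 SD

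The larger shift is 0.128/0.341 = 38% of the reference difference. ANCOVA removes it under the linear model.

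These ratios are for the t test. They do not carry over exactly to the rank-sum test, which also makes no use of baseline unless it is run on changes.

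**The case against.** The strongest reply is that nothing here is invalid. Under 1:1 randomisation both unadjusted tests keep their error rate, and that rate already allows for chance imbalance. This stands, and it limits the point to efficiency on secondary outcomes.

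Second, the article is condensed, and covariates for secondary models are often left to an analysis plan that is not shown. That would answer a complaint about missing detail. Here, however, a test is named, and adjustment is named for a different outcome in the same section. An analysis plan that followed this text would carry the weakness forward.

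Third, the gain rests on an assumed r, with one range applied to hormones, neurotransmitters and questionnaires alike. At r = 0.3 the gain over post values is small (80% to 83.6% power), and at r = 0.8 the gain over change is negligible (99.3% to 99.7%). This is fair, and it is why the whole range is shown.

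A reader might also infer stronger claims that the documents do not support:

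- *That the baseline values are discarded.* The analysed quantity is not stated, and the title "The change of ovarian reserve function" suggests change scores for those markers, which do use baseline.
- *That selecting women with low AMH or AFC biases a change comparison through regression to the mean.* Selection comes before randomisation and moves both arms alike in expectation. Only chance imbalance remains.
- *That power is lowest for ovarian reserve.* The article compares power across no outcomes, and the same tests are named for outcomes without a week-0 value.

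**Conclusion.** The point holds as one of efficiency. For continuous secondary outcomes with a week-0 value, the named tests either ignore baseline or use it suboptimally, and they leave out centre, although the plan uses both for its primary outcome. A better method is available with data the trial already collects.

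The size depends on r, which the article does not give. Over the assumed 0.3 to 0.8, with equal variances, the avoidable variance is 9% to 64% if post-treatment values are compared and 10% to 35% if changes are compared. For ovarian reserve the second range is the better supported one, because of the section title.

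The primary outcome is untouched, as are outcomes with no pre-treatment value, such as oocyte number, embryo counts, gonadotropin dose and MASS. It should be changed, but the trial's validity does not depend on it.

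**What to change.** In Statistical methods, or in the analysis plan before unblinding, replace the unadjusted test for each continuous outcome with a week-0 value by ANCOVA:

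- the post-treatment value as response, with arm, the week-0 value of the same variable and centre as covariates;
- a log or rank transformation where the distribution is skewed, with the rule for choosing it stated in advance;
- the adjusted difference, or ratio on the log scale, reported with its 95% confidence interval.

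Keep the t or rank-sum test for outcomes without a baseline value, such as number of oocytes. Once the post-treatment value is named as the response, the question of post value or change is also settled; the treatment effect is the same whichever is modelled, provided baseline is in the model on the same scale.

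The cost is a change of wording and a routine model in the software already named. It needs no new data, visits or participants.
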